### ***Cardiorespiratory fitness & body composition (see Section 4.6) (if permitted)***

Participants will be asked to attend the Be Active Sleep Eat (BASE) Facility at Monash University to undergo submaximal cardiorespiratory fitness assessment and a DEXA scan to assess body composition assessment at baseline and 3-month follow-up.

### ***University of Melbourne laboratory-based outcomes (see Section 4.6) (if permitted)***

At baseline, laboratory-based secondary outcomes will be collected in the CHESM laboratory. At 3-month follow-up, participants will be asked to return to the CHESM laboratory to complete the secondary outcomes. Some of the measures outlined are opt-in.

### ***Inflammatory outcomes (see Section 4.6) (if permitted)***

At baseline, participants will be asked if they agree to opt-in to have a blood sample taken at any of the Melbourne Pathology centres. The blood will be stored at Melbourne Pathology and analysed for inflammatory markers. At 3-month follow-up participants will be asked to return to Melbourne Pathology to have another sample of blood taken.

## 8. INTERVENTION

This 9-month study includes 3-month exercise programs delivered by a physiotherapist followed by a continuation of the exercise program independently for a further 6 months. Participants in both groups will attend 9 online treatment sessions via Zoom, over the first 3 months. Once per week over the first 6 weeks and fortnightly thereafter. The first session will be up to one hour with subsequent sessions up to 30 minutes. Physiotherapists will provide participants with home-based strengthening exercises in paper format, containing exercise instructions. Participants in both groups will be prescribed exercise dosage (i.e. frequency, intensity, time) according to the American College of Sports Medicine (ACSM) recommendations. A 2017 meta-analysis in this area demonstrated that exercise programs prescribed in accordance with ACSM dosage recommendations resulted in greater symptom improvement compared to exercise programs with questionable concordance to ACSM dosage recommendations. Feasibility and acceptability of aerobic and strengthening exercise prescribed according to ACSM dosage recommendations has been demonstrated in our recent pilot study (HREC. 1851762). Participants will be provided with an ankle-cuff weight and resistance bands. Participants will also receive a wearable activity monitor to wear daily for the initial 3 months of the study.

**Strengthening only:** Participants will be instructed by the physiotherapist how to perform 5-6 lower limb strengthening exercises, including how to use equipment such as ankle cuff weights and exercise resistance bands. Initial sessions will involve 1 to 2 sets of 8 to 12 repetitions at an intensity deemed by the participant to be at least 'hard' ( $\leq 7$ ) on the modified Borg Scale of rating of perceived exertion (RPE). The dosage will increase as appropriate to 3 sets at 'hard to very hard' (between 7 to 8) on modified RPE Borg Scale (*Modified Borg Scale; 10 is maximal effort*). Strengthening exercises will take approximately 30 minutes per session. Participants will be asked to complete these three times per week at home.

**Aerobic & strengthening:** Participants will be prescribed muscle strengthening exercise as above. They will also be facilitated to build up to engaging in 150 minutes of moderate intensity aerobic exercise per week, which will be tailored to individual preferences, including a choice of activities such as walking, cycling and swimming. Participants will be encouraged to incorporate exercise into their daily lives and guided to gradually increase their aerobic activity to a moderate intensity of 30 minutes, 5 days a week with blocks of at least 10 minutes being appropriate. Physiotherapists will guide participants to self-monitor their aerobic exercise at a moderate intensity equivalent to at least 'somewhat hard' on the Borg RPE Scale (13-14) and corresponding heart rate, monitored on a wearable heart-rate sensor.

Following 3 months of guided exercise by the physiotherapists, participants will be encouraged to maintain the exercise program over the subsequent 6 months unguided.

**Physiotherapists:** We will recruit approximately 8 practising musculoskeletal physiotherapists in metropolitan Melbourne to deliver interventions for the trial on Independent Contractor Agreements. The same therapists will deliver intervention to both groups online via Zoom. The intervention will be protocolised. Participants will be randomly allocated to a physiotherapist.

To be eligible to deliver the intervention in this clinical trial, physiotherapists must:

- hold current registration to practice as a physiotherapist;
- have a receptionist at their clinical practice to facilitate patient booking and communication with research staff;
- have an Australian Business Number;
- be willing to undertake trial training requirements (see below);
- be willing and able to deliver interventions between July 2019 and Sept 2022;
- practice around the metropolitan Melbourne area;
- have treated at least five individuals with hip OA in the past 12 months.

**Physiotherapist training**

Physiotherapists will be required to attend the University of Melbourne for a 4-hour training session. The training will address clinical trial procedures and treatments. Treatment manuals and copies of patient resources (e.g. exercise sheets and information brochures for handouts) will be provided to the physiotherapists in electronic and hard-copy. Physiotherapists will be provided with a Zoom Information Booklet that contains detailed step-by-step instructions on using Zoom. Physiotherapists will also receive personal assistance from the Trial Coordinator to ensure they are comfortable using the technology prior to their first online consult.

**Treatment fidelity:** Paper-based treatment notes from each consultation will be assessed by research staff for physiotherapist adherence to trial protocols. Fidelity will be recorded as the number and proportion of consultations where the RPE equalled or exceeded 'some-what hard' for aerobic component (i.e. 13-14 on the Borg RPE scale) and 'very hard' for the strengthening program (i.e. 7-8 on the modified Borg scale). The mean (SD) rating of perceived exertion for each participant's exercise program will be determined over their consultations, as recorded in the treatment notes.

**9. ADVERSE EVENT REPORTING**

Adverse events (AE's) are defined as any untoward medical occurrence in a clinical trial participant that does not necessarily have a causal relationship with the treatment. A related adverse event, or harm, is an adverse event that appears to be caused by the trial interventions.

Serious adverse events (SAE) are defined as any untoward medical occurrence that:

- Results in death,
- Is life-threatening
- Requires hospitalisation or prolongation of existing inpatients' hospitalisation,
- Results in persistent or significant disability or incapacity,
- Is a congenital anomaly or birth defect

Any other important medical condition which, although not included in the above, may require medical or surgical intervention to prevent one of the outcomes listed whether or not it is deemed related to the trial intervention.

A related adverse event will be defined as an adverse event that appears to be caused by the exercise programs. Participants who experience any related adverse events during the first 3 months will be instructed to discuss these with their project physiotherapist who will institute appropriate advice. Any adverse event that the physiotherapist feels unable to manage will be reported by the physiotherapist to the research team via the study email. Any risks to participants are likely to be minor and transient. All related adverse events during the first 3 months will be recorded by physiotherapists in the treatment notes. The study physiotherapist will be asked to return their treatment notes upon completing the 3-month study treatment and the research team will document these related adverse events from the treatment notes into the study adverse events log.

If participants experience any related adverse events as a result of performing the exercise programs unsupervised (3 to 9 months), they will be advised to contact the research team via the study email and a practising physiotherapist from the research team will advise the participant accordingly. The research team will document the related adverse events in the study adverse events log.

Participants will be asked about any non-related adverse events at 3 months and 9 months via a questionnaire. Participants will record the nature of reported adverse events, how long they lasted and what action they took (i.e. taking medication or seeing a health professional). The research team will document the non-related adverse events in the study adverse events log.

Participants will be advised to report any serious adverse events (incapacitating, life-threatening, hospitalisation or death) to the Trial Coordinator as soon as they can by telephone, which will be documented. Any adverse events reported by telephone (by either the participant and/or the physiotherapist) will be reported to the internal trial monitoring committee (The Principal Investigator, the Trial Coordinator and at least one other Investigator who will meet fortnightly to monitor the progress of the trial), who will be responsible for deciding what action, if any, is needed on a case by case basis. Due to the low-risk nature of the interventions in this trial, serious adverse events are extremely unlikely but will be reported to the Sponsor's Ethics Committee should they occur.

Serious adverse events (SAEs) will be reported to the Chief Investigator within 24 hours of the research team becoming aware of them, and the Chief Investigator will determine causality and expectedness. SAEs deemed unexpected and related to the trial will be reported to the research ethics committee within 72 hours using the Serious Adverse Event Form. All participants experiencing serious adverse events will be followed-up as per protocol until the end of the study period (i.e. 9 months). All recorded adverse events will be reported to the Trial Management Committee as blinded data at the monthly meetings.

Related adverse events are expected to be minimal given that previous trials have investigated a combination of aerobic and strengthening exercise in people with hip osteoarthritis and reported no serious adverse events. Adverse events that may be expected as part of the interventions or usual care, which do not need to be reported immediately to the HREC include: transient increase in hip pain, stiffness and swelling or delayed onset muscle soreness due to increased exercise or physical activity. There are no serious adverse events that are expected for the interventions in this study.

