### 1.4 Internal Trial Committees

The Principal Investigator, the Trial Coordinator and at least one other Associate Investigator will meet fortnightly to monitor progress of the trial (Trial Management Committee), including any participant reports of adverse events.

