|-------------------------------------------------------------------------------------------------------|----------------------------------------------------------------------------------------------------------------------------------------------------------------------------------------------------------------------------|----------------------------------------------------------------------------------------------------------------------------------------------------------------------------------------------------------------------------------|---------------------------------|
|                                                                                                       | indicate the frequency of use (over the past 6 months) of a range of pain and arthritis medications and co-interventions.                                                                                                  | drug/supplement at least once a week in the past month will be reported as a current user of the relevant medication. Participants who have used a co-intervention once in the past 6 months will be reported as a current user. |                                 |
| Adverse events                                                                                        | Recorded by participants using a custom-developed table.                                                                                                                                                                   | Proportions of participants experiencing adverse events will be reported.                                                                                                                                                        | 3 months and 9 months           |
| Expectation of treatment outcome                                                                      | Rated using a Likert scale with anchors of “no effect at all” to “complete recovery”                                                                                                                                       | The number and proportion of participants selecting each response option will be reported.                                                                                                                                       | Baseline                        |

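### Sections 4.6 and 9 disagree on whether the 3- and 9-month adverse event questions cover all events, and under section 9 related events have no scheduled prompt in months 3 to 9

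*Protocol*

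**What the plan says.** Protocol section 4.6 lists adverse events among the secondary outcomes at 3 and 9 months. The source is given as "Recorded by participants using a custom-developed table" and the summary as "Proportions of participants experiencing adverse events will be reported". Neither entry restricts the events by cause.

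Protocol section 9 divides collection by perceived cause:

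- **Unrelated events:** "Participants will be asked about any non-related adverse events at 3 months and 9 months via a questionnaire".
- **Related events, months 0 to 3:** "Participants who experience any related adverse events during the first 3 months will be instructed to discuss these with their project physiotherapist". The physiotherapist records them in the treatment notes. On timing, "The study physiotherapist will be asked to return their treatment notes upon completing the 3-month study treatment", and the research team then copies the events into the adverse events log.
- **Related events, months 3 to 9:** for events arising from unsupervised exercise, "they will be advised to contact the research team via the study email".

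On oversight, section 1.4 says that the Trial Management Committee "will meet fortnightly to monitor progress of the trial". Section 9 repeats the fortnightly interval in one sentence, but later states: "All recorded adverse events will be reported to the Trial Management Committee as blinded data at the monthly meetings".

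**The concern.** The trial adds aerobic exercise, building up to 150 minutes a week, to a strengthening program that both arms receive. The harms of most interest are therefore those the exercise might cause. Under section 9 these are the events with no scheduled question, while events thought unrelated are asked about twice.

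Sorting by cause before collection also puts the causal judgement on the participant. The same sore knee might be blamed on the program by someone who has been walking briskly as prescribed, and put down to something else by someone doing strengthening only. The two reports would then travel by different routes with different chances of being recorded. In months 0 to 3 the record is made by physiotherapists who treat both arms, and so know what each participant receives, and who are unblinded to the hypotheses (sections 5.5 and 8). What is at stake is whether the reported proportions with adverse events can be compared between arms.

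**Working it through.** The protocol states no adverse event rate, capture rate or safety power, so there is no figure to reproduce. The check sets the sections side by side, with simple arithmetic on time.

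**1. Scope of the participant-recorded instrument**

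| | Section 4.6 | Section 9 |
|---|---|---|
| Recorded by | Participant | Participant |
| When | 3 and 9 months | 3 and 9 months |
| Events covered | Adverse events, no limit by cause | Non-related events |

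The timing and respondent match; the scope does not. Section 9 sends both streams to one log, so related events are not excluded from reporting by rule. But section 4.6 names the participant table as the source and does not mention the log, so it is unclear which source supplies the proportions.

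**2. Routes for related events under section 9**

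| Period | Route | Scheduled question? | First recorder |
|---|---|---|---|
| Months 0 to 3 | Raised with the physiotherapist | None stated, but 9 scheduled sessions | Unblinded physiotherapist |
| Months 3 to 9 | Participant emails the team | No | Research team, if contacted |

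Time with neither a scheduled session nor a scheduled question about related events: 9 − 3 = 6 months, or 6/9 = 67% of follow-up. Participants are encouraged to keep exercising unguided throughout this period (section 8).

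**3. Delay to the log, months 0 to 3**

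Section 8 gives weekly sessions for 6 weeks, then fortnightly sessions, over a 12-week program. Assume that the notes come back promptly at week 12. An event *w* weeks into treatment then waits 12 − *w* weeks:

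- first week (*w* from 0 to 1): 12 to 11 weeks, which is 12/2 = 6 to 11/2 = 5.5 fortnightly intervals (5 to 6 meetings), or about 3 monthly meetings;
- *w* = 6: 6 weeks;
- *w* = 12: no wait.

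This applies only to non-serious related events that the physiotherapist manages and nobody telephones in. Section 9 gives three faster routes. Events the physiotherapist feels unable to manage are emailed to the team. Events reported by telephone go to the committee. Serious events are to be telephoned in as soon as possible and reach the Chief Investigator within 24 hours of the team learning of them.

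**4. Committee interval**

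It is fortnightly in section 1.4 and in one sentence of section 9, and monthly in another sentence of section 9. Neither interval fits a log entry that waits for the end of treatment.

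**The case against.** The best defence is that section 4.6 already describes a participant-recorded table without restriction. The questionnaire is a listed attachment that is not shown, and it may ask about every event. This stands: it cannot be said that the instrument itself omits related events, only that section 9 describes it so and section 4.6 does not.

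Second, months 0 to 3 are well covered. Participants are instructed to raise related events, physiotherapists are to record all of them, and both arms have the same nine sessions with the same therapists. This also stands. The weakness in that period is recording that is unmasked and not standardised, rather than an absence of contact.

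Third, the delay concerns minor events in a trial the protocol regards as low-risk, and the committee receives blinded data. A reader might infer that related harms in general stay hidden from the committee during treatment. The faster routes rule that out.

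A reader might also infer that related harms will certainly be under-counted, or that the bias favours one arm. The protocol supports neither. It gives no event or capture rates, and participants, who do the first sorting for the questionnaire and email routes, are themselves blinded by limited disclosure. If capture were incomplete but equal in the two arms, absolute differences would shrink while the risk ratio stayed the same.

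The defence does not resolve the conflict between sections, nor does it supply a prompt for related events after month 3 if section 9 governs.

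**Conclusion.** The point holds as a contradiction with a practical consequence. Sections 4.6 and 9 give different scopes for the same 3- and 9-month collection. If section 9 is followed, related events go without a scheduled prompt for 6 of 9 months, their first record in months 0 to 3 is made by unblinded staff, and participants must attribute cause before reporting. Under-counting is most plausible in months 3 to 9. It remains an inference, and its size and any imbalance between arms cannot be calculated from the document. The late log entry, at most about 11 to 12 weeks and assuming prompt return of notes, is confined to non-serious, therapist-managed events. The fortnightly and monthly intervals are a separate inconsistency, largely editorial. The sample size and the primary analysis are unaffected.

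**What to change.** Reword section 9 to agree with section 4.6, so that the 3- and 9-month questionnaire asks every participant in both arms about all adverse events, whatever they think caused them. Have an existing team member who is masked to group assign relatedness afterwards, using the definition already in section 9. State that the reported proportions come from the log after questionnaire, email and therapist reports are merged. Give one committee interval in sections 1.4 and 9, and bring the time at which therapist-recorded events enter the log into line with it.

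The cost is questionnaire wording and a short amendment to section 9, with no extra visits or participants. The small downside is that the same event may arrive from both the therapist and the questionnaire, so duplicates have to be reconciled.

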### **9.1 Specific Safety Considerations (E.g. Radiation, Toxicity)**

Participants will be exposed to small amounts of radiation through acquisition of the DEXA scans (baseline and follow-up) and hip x-ray (baseline only, and only if participant does not have hip x-ray within past 12 months). As part of everyday living, everyone is exposed to naturally occurring background radiation and receives a dose of about 2 millisievert (mSv) each year. The additional effective dose participants will receive from entering this trial is approximately 0.6mSv. At this dose level, no harmful effects of radiation have been demonstrated as any effect is too small to measure. The risk is believed to be very low.

## **10. STATISTICAL METHODS**

### **10.1 Sample Size Estimation**

Primary endpoints of the trial are between-group differences in change in average overall hip pain intensity and change in physical function (Western Ontario and McMaster Universities Osteoarthritis Index) at 3 months. In OA trials, the minimum clinically important difference is a change in pain of 1.8 units (out of 10) and change physical function of 6 units (out of 68). Based on our recently completed RCT in hip OA, we assume a between-participant standard deviation of 2.2 for pain and 13 units for physical function and a baseline to follow-up correlation of 0.46 for pain and 0.40 for physical function. To achieve 90% power and 5% significance level we require 83 participants per group. Allowing for a 15% loss to follow-up rate (informed by previous hip OA trials), we aim to randomise a total of 196 participants over a period of 30 months.

### **10.2 Population to be analysed**

See section 5.2 Eligibility Criteria

### **10.3 Statistical Analysis Plan**

[name] will analyse the data in a blinded manner. Main comparative analyses between-group will be performed using intention-to-treat. Multiple imputation will be used to account for missing data if >5% of data are missing. For the primary hypothesis, difference in mean change in pain and function (baseline minus follow-up) will be compared between groups using linear regression models adjusting for baseline values, with random effects to account for clustering by therapist. Similar analyses will be conducted for continuous secondary outcomes. Perceived ratings of change will be compared using a logistic regression model with random effect for therapist. A sensitivity analysis will estimate treatment effects assuming full adherence, using a two-stage least squares approach. Effect of patient characteristics on outcomes will be explored by including relevant terms in the models. Standard diagnostic plots will verify model assumptions.

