|                       | 
Analysis Plan: A biostatistician will analyse blinded data. Main comparative analyses between groups will be performed using intention-to-treat. If there is >5% missing data, multiple imputation will be used to account for missing data. For the primary hypothesis, difference in mean change in pain and function (baseline minus follow-up) will be compared between groups using linear regression models adjusting for baseline values, with random effects to account for clustering by therapist. Similar analyses will be conducted for continuous secondary outcomes. Improvement based on global change will be compared across groups using risk differences, calculated from fitted logistic regression models. A sensitivity analysis will estimate treatment effects assuming full adherence, using a two-stage least squares approach. Effects of patient characteristics on outcomes will be explored by including relevant terms in models. Standard diagnostic plots will be used to check model assumptions. Effect modification by pre-specified baseline characteristics will be assessed through the inclusion of appropriate interaction terms in the regression models for the primary outcome. Mechanisms in accordance to pre-specified variables will be assessed using causal mediation analysis.
 |

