| Physical function subscale of the Western Ontario & McMaster Universities Osteoarthritis Index (WOMAC)  | Scored using 17 questions regarding hip function in the last 48 hours with Likert response options ranging from None to Extreme.                                                                                                                        | Total score ranges from 0 to 68; higher scores indicate worse function.                                                                                                                                      | Baseline, 3 months and 9 months |
| Secondary Outcomes                                                                                            |                                                                                                                                                                                                                                                         |                                                                                                                                                                                                              |                                 |
| Global improvement in:
a) Hip pain,
b) Physical function                                                       | Scored using a 7-point global rating of change Likert scale from with response options ranging from “much worse” to “much better” when compared to baseline.                                                                                            | Participants who indicate that they are “moderately better” or “much better” will be classified as improved. All other respondents will be classified as not improved.                                       | 3 months and 9 months           |
| Patient specific functional scale                                                                                    | Up to five activities of daily living are identified and scored on an 11-point NRS to record if performance was limited in the previous week.                                                                                                           | Ranges from 0 to 10; where 0=unable to perform and 10=able to perform the activity at the same level as before hip osteoarthritis. Higher scores indicate better function.                                   | Baseline, 3 months and 9 months |

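### The logistic model for global change names no baseline covariate; adding baseline pain or function would cost almost nothing and may gain zero to modest precision

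*Protocol*

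**What the plan says.** Protocol section 10.3 describes the effect models one after another. The two primary outcomes use "linear regression models adjusting for baseline values, with random effects to account for clustering by therapist". For the rest of the continuous outcomes, "Similar analyses will be conducted for continuous secondary outcomes". The global ratings then get their own sentence: "Perceived ratings of change will be compared using a logistic regression model with random effect for therapist". The therapist term is carried over; a baseline term is not mentioned.

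The synopsis names the effect measure for the same outcomes, again without covariates: "Improvement based on global change will be compared across groups using risk differences, calculated from fitted logistic regression models".

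Section 10.3 also says "Effect of patient characteristics on outcomes will be explored by including relevant terms in the models". That line is exploratory and sets no covariate for the main comparison.

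Section 4.6 defines global improvement, separately for hip pain and for physical function, as a 7-point transition rating against baseline at 3 and 9 months. It is split into improved (the two best categories) and not improved: "All other respondents will be classified as not improved". The same table lists overall pain NRS and WOMAC function at baseline. Under section 5.4, participants are enrolled only once the baseline questionnaire is complete, and allocation is revealed after the baseline outcomes are in.

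**The concern.** A prognostic baseline covariate usually sharpens a randomised comparison. The plan uses this for its continuous outcomes but states a model without it for its dichotomised patient-rated improvement outcomes. The natural covariates are already collected, before allocation and from everyone enrolled. If baseline severity predicts the global rating, the stated model leaves that variation in the risk difference, together with any chance imbalance in severity between arms. Randomisation is stratified by therapist only, so it does not control such imbalance.

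What is at stake is the width of the interval and the power for secondary outcomes for which the protocol claims no power. The validity of the comparison is not in question.

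**Working it through.** **1. The plan's own figure.** Section 10.1 gives SD 2.2 (pain) and 13 (function), differences of 1.8 and 6, baseline to follow-up correlations of 0.46 and 0.40, 90% power and 5% significance (two-sided assumed). For an analysis adjusted for baseline, n per group = 2(1.960 + 1.282)² × SD²(1 − r²) / difference².
- Function: 2 × 10.51 × 169 × 0.84 / 36 = 82.9, so 83.
- Pain: 2 × 10.51 × 4.84 × 0.788 / 3.24 = 24.8, so 25.
- Dropout: 83 / 0.85 = 97.6, so 98 per arm and 196 in total.

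The stated figures reproduce, and the continuous analyses already count on baseline adjustment: without it, function would need 99 per group. The calculation says nothing about the global ratings. The protocol gives no improvement rate, power or baseline correlation for them.

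**2. What correlation is plausible between baseline score and rating?** The figures 0.46 and 0.40 relate baseline to follow-up on the same scale, not baseline to the global rating. Two further steps are needed to get from one to the other.
- Baseline with change (baseline minus follow-up). If both SDs are equal, the correlation is √((1 − r)/2): √(0.54/2) = 0.52 for pain and √(0.60/2) = 0.55 for function. If the baseline SD is smaller, it drops. Section 5.2.1 requires pain of at least 4, which truncates baseline pain. With an assumed baseline SD of 1.5 against 2.2 at follow-up and r = 0.46, the covariance is 2.25 − 1.518 = 0.732, the SD of change is √(2.25 + 4.84 − 3.036) = 2.013, and the correlation is 0.732 / (1.5 × 2.013) = 0.24.
- Change with rating. Assume 0.5 to 0.85. Multiplying through gives 0.52 × 0.5 = 0.26 up to 0.55 × 0.85 = 0.47 under equal SDs, and 0.24 × 0.5 = 0.12 to 0.24 × 0.85 = 0.20 for pain in the truncated example.

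A rating driven by current state alone would correlate with baseline at about 0.40 to 0.46 in the opposite direction, so a mixture of the two could fall near zero. A range of 0 to 0.5 is therefore a fair one to examine.

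**3. Effect of adjustment.** Simulation of 3,000 trials per setting, 83 per arm, assumed 40% versus 60% improved, with the binary outcome cut from a latent normal variable that correlates r with baseline. Logistic models were fitted with and without the baseline score. The adjusted risk difference was obtained by averaging predicted risks over the observed baseline values. No therapist effect was simulated.

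| r | Power without | Power with | Variance ratio of risk difference (with/without) |
|---|---|---|---|
| 0 | 0.748 | 0.740 | 1.01 |
| 0.1 | 0.744 | 0.743 | 1.01 |
| 0.2 | 0.737 | 0.746 | 0.97 |
| 0.3 | 0.733 | 0.753 | 0.94 |
| 0.4 | 0.745 | 0.780 | 0.90 |
| 0.5 | 0.746 | 0.810 | 0.83 |

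Each power figure has a simulation error of about √(0.75 × 0.25 / 3000) = 0.008, so differences of a point or less should not be read as real. As sample size, a variance ratio of 0.97 is worth 166/0.97 − 166 = 5 participants, 0.94 is worth 11, and 0.83 is worth 34.

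Other assumed rates give a similar picture. At 30% versus 50% the variance ratio runs from 1.01 to 0.86, and at 50% versus 70% from 1.00 to 0.83. The gain at r = 0.5 is then 7 to 8 power points.

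**4. Odds ratio against risk difference.** On the log odds scale, adjustment raises the standard error: from 0.319 to 0.321 at r = 0, and to 0.357 at r = 0.5. The log odds ratio moves too, from 0.82 to 0.99 at r = 0.5, so its ratio to the standard error still rises (0.823/0.319 = 2.58; 0.990/0.357 = 2.77).

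**The case against.** The case for leaving the text alone is substantial. Section 10.3 never says the model is unadjusted, and a covariate list for a secondary binary outcome is often left to the statistical analysis plan, which is not at hand. The global rating has no baseline value of its own, so the rule for the continuous outcomes does not carry over. The size of any gain rests on a correlation the protocol does not give, and adjustment widens the standard error of the log odds ratio.

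Most of this stands. A reader might infer that the plan contradicts itself because every other effect model uses baseline pain and function. It does not. The primary models use each outcome's own baseline, the other continuous outcomes most naturally use theirs, and the full-adherence analysis names no baseline covariate at all: "A sensitivity analysis will estimate treatment effects assuming full adherence, using a two-stage least squares approach". A reader might also infer that the protocol's own correlations prove that baseline predicts the rating. They do not: that needs equal SDs and an assumed link between rating and change.

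Two parts do not dispose of the point. Section 10.3 does state a specific model, with the therapist term and no other, so there is wording to improve. And the synopsis chooses the risk difference, so the larger standard error of the log odds ratio does not count against adjustment here.

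**Conclusion.** The point holds as a low-cost efficiency improvement for a secondary outcome. It is neither an error nor an inconsistency, and it would be wrong to infer bias: the unadjusted randomised comparison is valid. The primary analyses and the sample size are untouched.

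Over assumed correlations of 0 to 0.5, adjustment changes the variance of the standardised risk difference by about +1% to -17%. At 40% versus 60% improved, it changes power by about -1 to +6 points. There is essentially nothing to gain at 0.1 or below and a modest gain near 0.5. These figures assume 83 per arm with outcome data, the improvement rates shown and no therapist clustering. That the stated model names no baseline covariate is certain; the size of the benefit is not. The trade still favours adjustment, because the worst case costs about 1% in variance.

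**What to change.** In section 10.3 and in the synopsis, pre-specify baseline overall pain NRS as a covariate in the model for global change in pain, and baseline WOMAC function in the model for global change in function, at both 3 and 9 months. Keep the therapist effect. State that the risk difference is standardised over the observed baseline distribution, so that both places describe the same model and the same effect measure.

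The cost is one sentence in each place, with no new data and no extra participants. Fixing it before unblinding also removes any later choice of covariates.
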